## Abstract

**Background:**

Nonmuscle invasive bladder cancer (NMIBC) accounts for 75% of bladder cancers. It is common and costly. Cost and detriment to patient outcomes and quality of life are driven by high recurrence rates and the need for regular invasive surveillance and repeat treatments. There is evidence that the quality of the initial surgical procedure (transurethral resection of bladder tumor [TURBT]) and administration of postoperative bladder chemotherapy significantly reduce cancer recurrence rates and improve outcomes (cancer progression and mortality). There is surgeon-reported evidence that TURBT practice varies significantly across surgeons and sites. There is limited evidence from clinical trials of intravesical chemotherapy that NMIBC recurrence rate varies significantly between sites and that this cannot be accounted for by differences in patient, tumor, or adjuvant treatment factors, suggesting that how the surgery is performed may be a reason for the variation.

**Objective:**

This study primarily aims to determine if feedback on and education about surgical quality indicators can improve performance and secondarily if this can reduce cancer recurrence rates. Planned secondary analyses aim to determine what surgeon, operative, perioperative, institutional, and patient factors are associated with better achievement of TURBT quality indicators and NMIBC recurrence rates.

**Methods:**

This is an observational, international, multicenter study with an embedded cluster randomized trial of audit, feedback, and education. Sites will be included if they perform TURBT for NMIBC. The study has four phases: (1) site registration and usual practice survey; (2) retrospective audit; (3) randomization to audit, feedback, and education intervention or to no intervention; and (4) prospective audit. Local and national ethical and institutional approvals or exemptions will be obtained at each participating site.

**Results:**

The study has 4 coprimary outcomes, which are 4 evidence-based TURBT quality indicators: a surgical performance factor (detrusor muscle resection); an adjuvant treatment factor (intravesical chemotherapy administration); and 2 documentation factors (resection completeness and tumor features). A key secondary outcome is the early cancer recurrence rate. The intervention is a web-based surgical performance feedback dashboard with educational and practical resources for TURBT quality improvement. It will include anonymous site and surgeon-level peer comparison, a performance summary, and targets. The coprimary outcomes will be analyzed at the site level while recurrence rate will be analyzed at the patient level. The study was funded in October 2020 and began data collection in April 2021. As of January 2023, there were 220 hospitals participating and over 15,000 patient records. Projected data collection end date is June 30, 2023.

**Conclusions:**

This study aims to use a distributed collaborative model to deliver a site-level web-based performance feedback intervention to improve the quality of endoscopic bladder cancer surgery. The study is funded and projects to complete data collection in June 2023.

**Trial Registration:**

ClinicalTrials.org NCT05154084; https://clinicaltrials.gov/ct2/show/NCT05154084

**International Registered Report Identifier (IRRID):**

DERR1-10.2196/42254

## Introduction

### Background

Nonmuscle invasive bladder cancer (NMIBC) is a common disease with an incidence of 19.1 and 4.0 cases (men and women, respectively) per 100,000 person-years in the European Union [1]. Three-quarters of all new bladder cancer diagnoses are that of NMIBC [2]. This disease is the most expensive to manage, per patient, from diagnosis to death [3,4].

The standard of care management for all suspected NMIBC is surgical transurethral resection of bladder tumor (TURBT). Evidence guides how the initial TURBT should be performed and perioperative practice, including the use of single-instillation intravesical chemotherapy (SI-IVC) to reduce recurrence rates of cancer [5]. It has been proposed that achieving “good-quality” NMIBC surgery and perioperative practice results in reduced recurrence rates [6]. This evidence forms the basis for the recommendations made in guidelines including those by the European Association of Urology (EAU) [5], the American Urological Association (AUA) [7], and the National Institute for Health and Care Excellence (NICE) [8] in England and Wales. The usual NMIBC diagnosis and treatment pathway is shown in Figure 1.

**Figure 1 figure1:**
[figure not shown]
Nonmuscle invasive bladder cancer diagnosis and treatment pathway. TURBT: transurethral resection of bladder tumor.

### The Problem

Compliance with best practice for TURBT surgery and perioperative guidelines varies widely [9], which may impact oncological outcomes [10-12]. There is a significant variation in early tumor recurrence rates between different sites that cannot be accounted for by patient, tumor, or adjuvant treatment factors [10], suggesting surgical factors may be the cause. In a survey of practice in 9 European countries published in 2019, significant deviation from guidelines was identified even for interventions with high certainty of evidence, such as SI-IVC administration [9]. There has recently been a proposed set of “quality indicators” for TURBT but the published review acknowledged that there was a lack of evidence that implementing these quality indicators resulted in improved outcomes [13]. A long-running study on quality standards in TURBT surgery in Scotland demonstrated that being involved in a national audit and feedback program of TURBT quality performance indicators did lead to a trend in improvement of quality indicator achievement over time, but a critical limitation was that there was no control group or comparison to baseline performance [14,15]. This work also established the utility and measurability of certain TURBT quality indicators in the real world.

### The Intervention: Electronic Audit, Feedback, and Education

Audit and feedback have the potential to improve professional practice and impact patient outcomes. Meta-analyses of the effects of audit and feedback in health care demonstrate wide variation in effect size [16]. The median baseline performance–adjusted improvement in compliance with desired practice was 4.3% but varied from 0.5% to 16%. Further, there is theory and evidence that education on addressing deficiencies highlighted by audit may enhance the effectiveness of audit and feedback [17,18].

A systematic review concluded that feedback can improve surgical performance, but the strength of the conclusions was tempered by the heterogeneity, the lack of randomization, and the lack of controls in the included studies [15,19,20]. A systematic review of electronic audit and feedback interventions concluded that effects were variable and only 2 of 7 identified studies used theory to guide interventions [21].

For bladder cancer surgery, there are professional practice behaviors under the control of the surgeon that have proven to be associated with patient outcomes after TURBT surgery [6,22-25]. Given that audit, feedback, and education is a cost-effective and simple intervention and has demonstrated efficacy in other settings, we would hypothesize that this intervention also improves perioperative indicators of surgical quality. Furthermore, there is evidence that targeting “process measures” as the unit for change is more effective than targeting patient outcomes [26]. Therefore, we chose to target professional practice behaviors (or quality indicators) as the primary outcomes rather than a disease outcome such as recurrence rates.

### Objectives

#### Main Objective

The primary objective is to determine whether “audit, feedback, and education” improves achievement of TURBT quality indicators.

#### Other Objectives

The other objectives are to determine (1) if audit, feedback, and education improves the early recurrence rate of NMIBC after first TURBT; (2) if achievement of TURBT quality indicators is associated with early recurrence rate of NMIBC after the first TURBT; (3) the average and variation in achievement of TURBT surgery quality indicators and early recurrence rate across surgeons, sites, countries, and health care settings (site type and operating list type); and (4) associations among site, surgeon, and surgical factors and achievement of TURBT quality indicators and early recurrence rate.

## Methods

### Study Design

This is an international, observational, multicenter study with an embedded prospective cluster–cluster randomized, parallel-arm, superiority trial of audit, feedback, and education. A cluster randomized trial was chosen because intrasite contamination would be expected if randomization was at the clinician level. A cluster is defined as one or more hospitals within the same health care organization where the same surgeons perform TURBT surgery. Sites will be informed of any updates to the protocol or standard operating procedures with the latest trial documents available on the BURST RESECT study website (protocol version 4.0 November 11, 2020).

### Data Collection, Management, and Privacy

Data will be entered into a web-based secure database hosted at University College London (Research Electronic Data Capture [REDCap]). Collected data are anonymous. Case report forms were developed with peer review and national and international testing (tested in the United Kingdom, France, and the United States). Data range checks, data sense rules, and essential required variable alerts will be programed at outset to improve accuracy and completeness. In total, 10% of all records will be manually checked for sense and completeness. Manually identified errors will be coded as automated rules, and the whole database scanned or audited for errors. Identified errors will be alerted to sites for correction before database lock. Data errors and incomplete or missing follow-up data will be queried with sites on a patient-by-patient basis through a web-based data auditing app. The resection and single-instillation intravesical chemotherapy for nonmuscle invasive bladder cancer treatment study data analysis group comprising statisticians based at the University of Aberdeen will have access to the final data set.

### Ethical Considerations

Local and national ethical and institutional approval or exemption will be obtained at each participating site. In the United Kingdom, the University of Aberdeen deemed this study exempt from research ethical approval in line with health research authority guidelines. There is no compensation to sites associated with this study. The study will be published in peer-reviewed journals and presented at national and international scientific congresses. Individual sites or surgeons will not be identified in study reports or performance feedback.

### Inclusion and Exclusion Criteria

#### Site Inclusion and Exclusion Criteria

Sites anywhere in the world will be included if they perform TURBT for NMIBC and could include at least 20 consecutive eligible cases in a period of 12 months. Sites will be excluded if they fail to include 20 cases with a minimum required data set to determine baseline performance. Where a site requests removal from the study, data collected to date will be maintained for reporting purposes unless the site requests deletion.

#### TURBT Case Inclusion and Exclusion Criteria

Sites will include consecutive cases of first, curative intent, elective transurethral surgery for a new diagnosis of urothelial carcinoma, thought to be nonmuscle invasive at the time of surgery, across all surgeons at their site. Cases with known concurrent upper tract urothelial carcinoma will be excluded.

### Study Design

The study will have four phases, which are summarized in Figure 2: (1) phase 1: site registration, study agreements, and usual practice surveys; (2) phase 2: retrospective baseline data collection; (3) phase 3: randomization to either arm of “no intervention,” or “audit, feedback, and education”; and (4) phase 4: prospective data collection.

**Figure 2 figure2:**
[figure not shown]
Study phases and design. TURBT: transurethral resection of bladder tumor.

#### Site Registration, Study Agreements, Surgeon Registration, and Usual Practice Surveys

Sites will complete a survey about their location, hospital type, and their usual practice. An agreement will be signed by the site principal investigator including consent to randomization. Each surgeon performing TURBT at the site will be registered along with details about their surgical experience including their grade, number of TURBTs performed per month, and years of experience.

#### Baseline Data Collection

Sites will be asked to enter data about consecutive eligible TURBT cases performed at their site counting backward from the date of site registration. The rationale is to sample cases from before a site had awareness of the study to obtain a cohort free from the Hawthorne effect [27].

#### Randomization

Sites will be randomized 1:1 in parallel arms when the submission of the minimum required retrospective data is complete. Sites will be randomized to either (1) no intervention (the site continues to submit data on consecutive eligible cases but without performance feedback and education during the study). Once the study is complete, these sites will be provided with performance and education feedback or (2) audit, feedback, and education (performance feedback and education provided before beginning further prospective phase of study).

Sites will be randomized using the randomization app at the Centre for Healthcare Randomised Trials (CHaRT), University of Aberdeen, which developed the randomization sequence. This randomization app is available 24 hours a day, 7 days a week as a web-based app. Randomization will be minimized for site-level variables that are thought to significantly impact achievement of TURBT quality indicators. There is no blocking. These are baseline performance from the baseline audit, geographical region (continent, except that the United Kingdom is considered alone, Australia will be combined with mainland Europe), and the presence of an existing TURBT audit at that site before the study. In addition, a random component is used in the minimization algorithm to ensure concealment of the allocation.

The study administrator will access the web-based system. They will enter the minimization variables into the web-based system, which returns the allocation status. The chief investigator of the site will be informed of their allocation following randomization. There is no blinding. To prevent contamination following randomization, sites randomized to no intervention will not be granted access to the dedicated personalized feedback and education resources, which are username and password protected.

#### Data Management

Local data will be routinely collected health care data accessed by members of the clinical team. Nonidentifiable data will be manually entered into the secure, password-protected study database (hosted at University College London) after appropriate local approvals have been obtained. Only the study management and statistical team will have access to the full data set.

## Results

### Audit, Feedback, and Education Design

The audit, feedback, and education intervention was designed using evidence-based theories about interventions that cause behavior change. These theories were both general [16,18,28-31] and specific to TURBT surgery based on our previous work [12,32].

The intervention is delivered at the site level with recommendations about how to engage with, disseminate, and use the feedback and education. There is no mandated change to clinician behavior or patient care, all patient treatment and professional practice decisions are at the discretion of the clinician. Sites can request to leave the study at any time, and all withdrawals will be reported. It will not be permitted for a site allocated to “no intervention” to receive the intervention during the study period.

Our group previously used qualitative methods to assess barriers and facilitators to a coprimary outcome for this study: SI-IVC administration [32]. The data from this qualitative study and a systematic review of barriers to NMIBC guideline compliance [12] were used to identify intervention functions and behavior change techniques (BCTs) using the theoretical domains framework, as suggested in the implementation science literature [29,30,33].

Conclusions from systematic reviews and expert groups about improving effectiveness of audit and feedback were used to inform the design of the feedback and education. For example: “feedback may be more effective when baseline performance is low [16]”; “if the source is a supervisor or colleague [16]”; “it is delivered in both verbal and written formats [16]”; “it includes both explicit targets and an action plan [16]”; and “process of care measures are more positively influenced by feedback than outcome of care [26].” In addition, adding education to feedback may enhance the effectiveness of audit and feedback and so this strategy will be adopted [17]: “audit and feedback interventions will be more effective when recommendations related to the audit and feedback are based on good quality evidence” [18] and if it “creates opportunity to learn [18].”

The design of the feedback is further informed by Brehaut et al’s [34] “15 suggestions for optimising effectiveness” of practice feedback interventions, the Clinical Performance Feedback Intervention Theory [31], and Colquhoun et al’s [18] “Theory Informed Hypotheses” for improving effectiveness of audit and feedback.

Finally, the study steering group applied the APEASE (Affordability, Practicability, Effectiveness and Cost-effectiveness, Affordability, Side-effects, Equity) [29] criteria to the possible BCTs. This process highlighted suitable BCTs and feedback and education components detailed in Table 1.

The performance feedback will take the form of a web-based feedback dashboard that will be freely available at any time to those given access as well as a report of the individual cases that make up their performance outcomes and other components. The components of the feedback dashboard are described in Table 1 and Figure 3 and displayed in Figure 4.

The study team or lead investigator will receive an email detailing the feedback and education intervention. They will be asked to forward the email and feedback and education dashboard access to all the surgeons at their site and present and discuss the feedback at a departmental meeting. The lead investigator must then complete a survey about how the feedback and education were used and disseminated at their site and any specific changes they have made (Figure 3).

**Table 1 table1:** Feedback and education intervention components, behavioral change techniques, theories, and mode of delivery.

Component		Description	Behavior change technique [30] or audit and feedback effectiveness theories or evidence	Mode of delivery
**Performance feedback**				
	1. Peer-comparison graphs	“Rate of achievement” scatter graphs displayed at both the site and surgeon level. All sites and surgeons are displayed but are anonymous, only current site data points are labeled with anonymous unique ID. Filterable by tumor grade.	Social comparison (6.2), “for those with a mastery goal orientation” feedback will be more effective if it involves comparison to others [18].	Web-based data dashboard, accessed via link in feedback email with site-specific passcode.
	2. Performance statement	The site’s level of achievement, the average level of achievement, the target, and whether they are considered above or below an explicit target. This is based on the experience of the Scottish Quality Performance Indicator programme [15].	Social comparison (6.2), Explicit target given [16].	In feedback email and displayed alongside peer-comparison graphs on web dashboard.
	3. Data description	An optional pop-up box described how the graphs were generated including the description of numerator and denominator, advice on interpretation, justification of quality indicator selection, target and case selection.	Theory of trust or credibility and nature of the data [18].	An optional pop-up box alongside each peer-comparison graph in the web dashboard.
	4. Action plan	Actions specific to each behavior provided, for example, an operative recording proforma to improve documentation outcomes.	Instruction on how to perform the behavior (4.1), restructuring the physical environment (12.1), adding objects to the environment (12.5), prompts or cues (7.1).	Displayed beneath the peer-comparison graph of each quality indicator with links to either written resources or to download the operative proforma.
	5. Individual case report	The cases analyzed for each quality indicator, along with selected clinically relevant variables (eg, tumor details and operating surgeon code) can be reviewed in a filterable report, and individual database records easily entered for case review and discussion.	Theory of feedback specificity, user-guided experience, and social engagement [18].	The site-specific reports are available in the study REDCap^a^ database environment, instructions about how to use are included in the feedback email and dashboard.
	6. Provide feedback more than once	The feedback dashboard is available throughout and displays live performance. Sites will be encouraged to engage with this at a departmental level regularly. Feedback email is resent encouraging ongoing feedback engagement every 2 weeks.	Provide multiple instances of feedback [34].	Same delivery method.

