**Figure 4 figure4:**
[figure not shown]
Intervention and design. Web-based performance feedback and education dashboard—accessible to only sites in the intervention arm during the study. Numbers in the boxes relate to the components in Table 1.

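### Only intervention sites see which of their cases count in their live score and can open those records; with no freeze of indicator fields described, revision of the coprimary outcomes may differ by arm

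*Protocol article*

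**What the plan says.** All references are to the protocol article.

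- **Case list and record access.** Table 1, component 5, gives sites a listing of the cases analyzed for each indicator. These "can be reviewed in a filterable report, and individual database records easily entered for case review and discussion". The listing sits in the outcome database itself: "The site-specific reports are available in the study REDCap^a^ database environment".
- **Score and target.** Component 2 tells a site "whether they are considered above or below an explicit target". Component 3 explains how the graphs are built, "including the description of numerator and denominator". Component 6 adds that "The feedback dashboard is available throughout and displays live performance", with the feedback email sent again every 2 weeks.
- **Arm restriction.** The Figure 4 legend describes the dashboard as "accessible to only sites in the intervention arm during the study". The Randomization section denies control sites the personalized feedback and education resources.
- **Ascertainment.** The Randomization section states: "There is no blinding". Under Data Management, local data are accessed by members of the clinical team and entered by hand.
- **Correction.** Under Data Collection, Management, and Privacy, 10% of records are checked manually for sense and completeness, errors found are turned into automated rules run over the whole database, and "Identified errors will be alerted to sites for correction before database lock". None of this is limited to one arm.
- **Denominators.** For every indicator, cases with the relevant field investigator-missing are excluded.
- **Analysis.** The site-level proportion is modeled with study arm, existing audit and baseline achievement as fixed effects. The intervention counts as effective if any one of the four coprimary outcomes improves significantly.

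**The concern.** A site that is shown its shortfall and the cases behind it has a reason to re-read the failures and none to re-read the successes. No misconduct is needed. If initial abstraction contains some honest errors in both directions, reviewing only the failures corrects those that count against the score and leaves those that flatter it. Control sites have neither the list nor the prompt, so their errors stay as first entered unless a central check finds them.

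The resulting gain in the measured rate cannot be told apart from better practice. The described manual check would not expose it, because a field changed from not achieved to achieved still passes a check for sense and completeness. The parallel control arm, on which the Discussion relies for the Hawthorne effect, does not remove it either, because the prompt is specific to one arm. The route is open for all four coprimary outcomes, and success on any one is enough.

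**Working it through.** **1. Reproduce the plan's figure.** Inputs from Sample Size: SD 0.2, difference 0.1, 90% power, 5% level (two-sided assumed; the article does not state it), 86 sites per arm. The normal approximation n = 2(1.960 + 1.282)² × 0.2² / 0.1² = 84.1 gives 85 per arm. With the noncentral t distribution, 85 per arm gives power 0.8999 and 86 gives 0.903. The planned 86 per arm (172 in all) reproduces and is not in dispute.

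**2. Shift from recoding prospective failures.** The SI-IVC mean is 0.651, so 1 − 0.651 = 0.349 of cases fail. If a share f of failed cases is recoded as achieved in the intervention arm alone, the between-arm difference moves by 0.349 × f. The documents give no value for f, so the table is a range and not an estimate.

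**3. Consequence with no true effect.** SE = 0.2 × √(2/86) = 0.0305. The chance of a significant result is 1 − Φ(1.96 − shift/SE) + Φ(−1.96 − shift/SE).

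| Assumed f | Shift | Chance of a significant result |
|---|---|---|
| 2% | 0.007 | 5.6% |
| 5% | 0.017 | 8.8% |
| 10% | 0.035 | 20.8% |
| 20% | 0.070 | 62.9% |
| 28.7% | 0.100 | 90.7% |

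The SE is that of an unadjusted comparison of site means. To the extent that baseline adjustment reduces it, the same shift would give a higher rejection rate.

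**4. Denominator route.** If failed entries become investigator-missing instead, the rate becomes 0.651 / (1 − 0.349f). For f = 10% this is 0.651 / 0.9651 = 0.6745, a shift of 0.0235 and a 12.1% chance of a significant result. For f = 20% the shift is 0.049 and the chance 36.0%.

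**5. Retrospective records.** Feedback starts before the prospective phase, so the first cases that an intervention site can review are its baseline cases. If these are revised upward after randomization and the revised values enter the model, the adjusted difference moves by −β × (baseline shift), where β is the slope of follow-up on baseline achievement. β is not given. With an assumed β between 0 and 1 and a baseline shift of 0.035, the movement lies between 0 and −0.035, against the intervention.

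**6. Yardsticks.** The planned detectable differences are 0.05, 0.075 and 0.10, depending on the indicator. The Introduction cites a median audit-and-feedback improvement of 4.3%. Steps 2 to 4 use the SI-IVC mean only, because the article gives no mean for the other indicators.

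**The case against.** A reader might infer that outcomes can be revised in one arm only, or that nothing makes correction symmetric. The article does not support this. The automated rules are run on the whole database, and alerts and record-by-record queries go to sites without regard to arm. Control records can be corrected too. What is one-sided is knowing which cases count against the score and being prompted to look at them.

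A reader might also infer that sites can freely edit outcomes through the case report until lock. That is not stated either. The stated purpose of opening records is review and discussion, correction is described for identified errors, and user rights are not given. They may be set out in the full protocol or a data management plan. This limits the point to a risk that the design creates and the text does not close. It does not remove the point, because the arm-specific list, live score and prompt are part of the stated design.

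The indicators are meant to be objective and come from the pathology report, patient record or operation note. An honest recoding therefore moves a record toward the truth, and the scope for honest recoding is bounded by the abstraction error rate, which is unknown. This stands as a limit on size. It does not restore balance, since correcting only failures in one arm still biases the comparison.

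Finally, the direction is not uniform: revised baseline records would work against the intervention, as step 5 shows.

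**Conclusion.** The point holds as a risk of differential outcome revision between arms. Control outcomes can also be corrected, and edit access through the case report remains an inference. One-sided revision of prospective failures would favor the intervention. Revision of retrospective records after randomization would tend to act against it.

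The size is unknown. If 10% of failed SI-IVC cases were recoded in the intervention arm alone, the shift would be about 3.5 percentage points, and a nominal 5% test with no true effect would be significant about 21% of the time. At 2% the effect is negligible (5.6%). These figures rest on the assumed share, the planning mean and SD, 86 sites per arm, a two-sided test and an unadjusted comparison. The feedback itself is not at fault. What is missing is a described safeguard between the feedback tool and the outcome data, and since the safeguard is cheap it should be added.

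**What to change.** 1. Lock the indicator fields of retrospective records at randomization, so that allocation cannot alter the baseline covariate.
2. Make a prospective case's completed indicator fields, including those that decide its eligibility for an indicator, read-only to the site before the case appears in the dashboard or case report. Filling a blank, such as late pathology, stays allowed.
3. Accept later changes only through the central query process already described, on the same criteria in both arms.
4. If locking is no longer possible, add a sensitivity analysis of each coprimary outcome on first-submitted values from the database change log (assumed to be kept), and report the number and direction of indicator edits by arm.

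The cost is a user-rights setting or, under item 4, one extra analysis and a short table. The dashboard, case list and departmental discussion stay as designed. The small downside is that genuine late corrections must go through a query.
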